#### Analysis of Primary Outcome

The primary outcome measure (ie, presence of depression diagnosis) is dichotomous and will be tested with logistic regression analyses comparing the percentage of depressive disorders in the D(o)epression Blended condition in this study to the percentage of depressive disorders in the D(o)epression face-to-face condition and the TAU condition from the previous RCT.

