### Intervention

D(o)epression Blended [22] is an adaptation of the Dutch D(o)epression face-to-face program [24]. D(o)epression face-to-face is an individual CBT program based on the evidence-based treatment program Coping with Depression course for Adolescents [24]. All 15 sessions of the original D(o)epression face-to-face protocol were adapted for use in an online environment in four modules. Major adaptations included a shortening of the wording, more use of attractive visuals, and the possibility to interact online with the therapist. The online program can be combined with a minimum of 5 and maximum of 15 face-to-face sessions. The face-to-face sessions last 45 minutes each, and the adolescent and the therapist are present. Face-to-face sessions are scheduled when the adolescent starts with a new online module and at the end of the treatment, as is advised in the manual. More face-to-face sessions can be added when the therapist considers this helpful or necessary, with a maximum of 15. Additionally, there is unlimited contact between the adolescent and therapist through a chat function within the program. During the face-to-face contacts, online modules are introduced, the therapist invests in the therapeutic relationship, exercises are practiced, and suicide risk is examined. There are also two face-to-face contacts with the parents (when parents are involved): after 3 weeks and after the start of the fourth module. Parents receive psychoeducation, information about CBT, and suggestions on how parents can contribute to the treatment. All CBT therapists who will offer the D(o)epression Blended as treatment were trained by a registered clinical psychologist in how to provide blended treatment and in working with this specific blended treatment protocol in a 1-day training session.

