**Treatment characteristics**											
	Gender, age, experience, specialization of therapist	Therapy Procedure Checklist			x	x					
	Expectancy of treatment	Parent Expectancies for Therapy Scale	x	x		x					
	Previous treatments	Vragenlijst Eerdere Hulp en Interventies [History of Treatments]	x	x		x					
	Satisfaction treatment	Service Satisfaction Scale	x	x					x		
	Therapeutic alliance	Therapeutic Alliance Scale for Children	x		x		x	x	x		
	Cooperation with treatment	Cooperation With Treatment scale			x		x	x	x		
	Therapy questions	Therapy Questions			x		x	x	x		
	Treatment integrity	Observation			x				x		

^a^T0=baseline.

^b^T1=during the intervention after 5 weeks.

^c^T2=during the intervention after 10 weeks.

^d^T3=at 1 to 4 weeks postintervention.

^e^T4=at 6 months follow-up.

^f^T5=at 12 months follow-up.

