#### Preliminary Analyses

Possible baseline differences in demographic and diagnostic characteristics between the three conditions—(1) D(o)epression Blended condition, (2) D(o)epression face-to-face condition, and (3) TAU condition (the latter two conditions from the RCT, which has already been conducted)—will be checked by means of ANOVA, MANOVA, and chi-square analyses. If these variables show differences between the conditions, they will be entered as covariates in all models and regression models to test the effectiveness of the intervention.

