#### Analysis of Secondary Outcomes

The intervention impact on the secondary outcomes (depression symptoms, depression severity, depression improvement, quality of life, suicide risk, comorbidity) will be evaluated using linear mixed modeling with the baseline level of the concerning variable as the covariate.

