#### Cost-Effectiveness Analyses

A cost-effectiveness analysis will be conducted by comparing the costs and effects of the D(o)epression Blended condition in this study to the costs and effects and effects of D(o)epression face-to-face and TAU. The economic evaluation will be executed in accordance with the CHEERS (Consolidated Health Economic Evaluation Reporting Standards) Statement [50,51], which has been successfully executed previously in an economic evaluation of treatment of anxiety disorders in children [52]. The costs of blended CBT versus face-to-face CBT and TAU will be expressed in (1) incremental costs per adolescent with a depression in full remission (based on the K-SADS-PL) and (2) incremental costs per quality-adjusted life year (based on the EuroQol). To gain insight into the uncertainty surrounding subtotal and total costs, and due to highly skewed cost distributions, bootstrap simulations (1000 replications) will be conducted. Bootstrap simulations will be conducted to quantify the uncertainty around the incremental cost-effectiveness ratio [53], yielding information about the joint distribution of cost and effect differences. The bootstrapped cost-effectiveness ratios will be subsequently plotted in a cost-effectiveness plane. The bootstrapped incremental cost-effectiveness ratios will also be depicted in a cost-effectiveness acceptability curve showing the probability that a condition is cost-effective using a range of ceiling ratios. Also, sensitivity analyses will be performed to test the robustness of the results. The cost-effectiveness analyses will be done separately from a mental health perspective and a societal perspective over a period of 6 months and 1 year.

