### Strengths and Limitations

One of the strengths of this study is that it is carried out in mental health institutions and that the targeted population of this study consists of adolescents referred for treatment of their depressive disorder. Participants were not recruited for treatment for the purpose of this study. This means that conclusions from the results of this research can be generalized to real-life mental health care. Additionally, the study will be conducted in several mental health care centers in the Netherlands. Therefore, our findings will not be based on the results of only one mental health institution, which adds to the generalizability of the results. Another strength is that we will compare a blended CBT treatment protocol to active treatment conditions: face-to-face CBT and TAU. Moreover, assessments will be based on multiple informants (ie, adolescents, parents, and therapists).

This innovative blended treatment has considerable potential. It incorporates the positive characteristics of online interventions, such as high accessibility, and the potential to be easily tailored to the daily lives of adolescents. To our knowledge, this is the first study on the effectiveness of blended CBT treatment of depressive disorders in adolescents. Therefore, we can uniquely contribute to the crucial evidence-based improvement of treatment protocols in mental health care.

A limitation is that the study is not designed as an RCT. In this study, we will recruit participants for the blended CBT condition only. The results of these participants will be compared with participants recruited in the earlier conducted RCT, in which face-to-face CBT was compared to TAU. Since there is no randomization in the current trial, it cannot be ruled out that there are slight differences in the participants, therapists, or societal context. We will try to keep this potential threat to internal validity as low as possible by working with the same inclusion and exclusion criteria for participants and with the same or similar mental health institutions. However, this pragmatic quasi-experimental design will deliver preliminary evidence and very relevant information on the effectiveness and cost-effectiveness of blended CBT in routine care.

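### The stated primary logistic model does not account for patients who share a therapist; if therapists treat several patients each and their outcomes are correlated, its confidence intervals would be too narrow.

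*Protocol article*

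**What the plan says.** - **Primary model** (Analysis of Primary Outcome). Presence of a diagnosis "will be tested with logistic regression analyses comparing the percentage of depressive disorders in the D(o)epression Blended condition" with the two conditions of the earlier RCT. No random effect, cluster term or robust variance is named.
- **Terms that may be added** (Preliminary Analyses). Demographic and diagnostic characteristics are compared between conditions. "If these variables show differences between the conditions, they will be entered as covariates in all models and regression models". Therapist and institution are not among these variables.
- **Delivery** (Intervention). For blended CBT, "The face-to-face sessions last 45 minutes each, and the adolescent and the therapist are present". A patient has between 5 and 15 such sessions plus chat, and the therapist may add sessions up to the maximum. "All CBT therapists who will offer the D(o)epression Blended as treatment were trained by a registered clinical psychologist".
- **Therapist data** (Table 1). The baseline items include "Gender, age, experience, specialization of therapist", and therapists complete several rating scales during treatment.
- **Secondary outcomes** (Analysis of Secondary Outcomes). These "will be evaluated using linear mixed modeling with the baseline level of the concerning variable as the covariate". The random effects are not stated.
- **Costs** (Cost-Effectiveness Analyses). For uncertainty, "bootstrap simulations (1000 replications) will be conducted". The resampling unit is not stated.
- **Limitations** (Strengths and Limitations). Without randomization, "it cannot be ruled out that there are slight differences in the participants, therapists, or societal context".

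**The concern.** Patients treated by the same therapist share that therapist's skill, style and use of optional sessions, so their outcomes tend to be correlated. Ordinary logistic regression takes every patient as an independent observation. Where several patients share a therapist and the correlation is positive, it understates the standard error of the treatment contrast.

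The contrast is exposed because the blended arm is a new cohort with specially trained CBT therapists, TAU comes from an earlier trial, and CBT was barred within TAU. Therapists are therefore probably nested largely within condition, and their effects would not cancel from blended CBT against TAU. This nesting is an inference; the article does not state it.

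At stake is the error rate of the main hypothesis test, blended CBT against TAU. Enrollment has closed and the recruitment section reports 42 patients, against 44 in each comparator, so a borderline result could turn on a modest change in the standard error. This is a matter of variance. It is separate from bias due to non-random allocation.

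**Working it through.** **1. The plan's own sample size.** Inputs from Sample Size: effect size 0.53, alpha 0.05 (taken as two-sided), power 0.80, dropout 20%.

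n per arm = 2 × (1.960 + 0.842)² / 0.53² = 55.9, rounded up to 56. With dropout, 56 / 0.80 = 70.

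This matches the stated 70 exactly. There is no allowance for clustering in it (design effect 1).

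**2. Inputs for the clustering check.** The number of therapists, the patients per therapist (m) and the ICC are not in the article, so they are assumptions:
- m from 1 to 4.7. The upper value is 42 recruited / 9 institutions = 4.7 patients per institution. It equals patients per therapist only if each site has one therapist, so it lies toward the high end.
- ICC 0.05 and 0.10.
- The same m and ICC in both arms being compared.

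**3. Formulas.**
- Design effect DE = 1 + (m − 1) × ICC.
- Correct interval width relative to the naive one = √DE.
- Shortfall of the naive standard error = 1 − 1/√DE.
- True two-sided error of a nominal 5% test = 2 × [1 − Φ(1.96/√DE)].

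**4. Results.**

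| m | ICC | DE | Correct interval wider by | Naive SE too small by | True error rate |
|---|---|---|---|---|---|
| 1 | any | 1.00 | 0% | 0% | 5.0% |
| 2 | 0.05 | 1.05 | 2.5% | 2.4% | 5.6% |
| 2 | 0.10 | 1.10 | 4.9% | 4.7% | 6.2% |
| 3 | 0.05 | 1.10 | 4.9% | 4.7% | 6.2% |
| 3 | 0.10 | 1.20 | 9.5% | 8.7% | 7.4% |
| 4.7 | 0.05 | 1.185 | 8.9% | 8.1% | 7.2% |
| 4.7 | 0.10 | 1.37 | 17.0% | 14.6% | 9.4% |

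**5. Cross-check by simulation.** A random-intercept logistic model with 42 against 44 patients, a 35% diagnosis rate (assumed), 3 to 5 patients per therapist in both arms and an unclustered two-proportion test gave error rates of 5.9–6.8% at ICC 0.05 and 6.7–8.5% at ICC 0.10. A repeat run agreed within 0.3 percentage points.

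**6. If only the blended arm is clustered.** With equal outcome variance per patient in the two arms, the worst case becomes (1.37/42 + 1/44) / (1/42 + 1/44) = 1.19. Intervals would be √1.19 − 1 = 9% wider and the error rate about 7.2%.

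**The case against.** The strongest reply is that this is a condensed article without its analysis plan. Variance estimators, random effects and resampling units often go there, and one sentence naming a model family does not exclude robust standard errors. This stands for the secondary outcomes and the bootstrap, where the structure is simply unstated. It is weaker for the primary outcome. There the article commits to a model and to a rule for which terms enter it, and following both as written gives an analysis that assumes independence.

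Four stronger readings are tempting, and the documents do not support them:

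- **That therapist is in no analysis model.** The mixed models do not state their random effects, so a therapist level is neither included nor excluded. The relationship with the therapist also enters the feasibility analyses under Other Analyses.
- **That the intervals are too narrow as a matter of fact.** This depends on m and the ICC, and neither is given. With one patient per therapist nothing is lost, and with two the loss is small.
- **That every arm is clustered by therapist.** TAU is described as a wide mix that includes medication, family therapy and running therapy. The article does not say that each TAU patient had one individual therapist, and it gives no therapist counts for the earlier RCT.
- **That the therapist is both treater and rater of the primary outcome.** The K-SADS interview is conducted by an independent research assistant. Rater correlation therefore concerns the therapist-rated secondary scales, and the larger ICCs that one might assume for such scales do not carry over to the diagnosis.

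**Conclusion.** The point holds in conditional form. The primary model as stated makes no allowance for shared therapists, although blended CBT is delivered by individual therapists. If therapists treat several patients each and the ICC is positive, the primary intervals would be too narrow and the test of blended CBT against TAU would reject too often.

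The size cannot be fixed from the article. Over the assumed range it runs from no effect to standard errors about 15% too small and an error rate of 9.4%. The top of that range needs about one therapist per institution, an ICC of 0.10 and equal clustering in both arms. It is worth correcting because the remedy is cheap and the comparison is small, but it is not a demonstrated error of known size.

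**What to change.** - **Analysis of Primary Outcome.** Keep the logistic model. State that standard errors will be cluster-robust with a small-sample correction and therapist as the cluster. Where therapist identity cannot be linked for the earlier RCT, use institution.
- **Analysis of Secondary Outcomes.** State that the linear mixed models include a therapist level.
- **Cost-Effectiveness Analyses.** State that the bootstrap resamples therapists with their patients, not single patients.
- **Reporting.** Give the number of therapists and the patients per therapist in each condition, so that readers can judge whether the correction matters.

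**Cost.** The change is to the analysis wording only, and follow-up was still under way when the article appeared. Intervals become modestly wider. The approach relies on therapist identity being recoverable for the earlier arms. Therapists completing forms makes that likely but does not prove it. If institution has to serve as the cluster, there are few clusters (nine institutions take part in the new cohort), so the small-sample correction is essential. Robust errors are preferable to a therapist random intercept for the primary outcome: with about 30 events (0.35 × 86, under the assumed diagnosis rate) and very small clusters, a random intercept may be unstable. If nearly every therapist treated a single patient, the result will hardly change.

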#### Analysis of Secondary Outcomes

The intervention impact on the secondary outcomes (depression symptoms, depression severity, depression improvement, quality of life, suicide risk, comorbidity) will be evaluated using linear mixed modeling with the baseline level of the concerning variable as the covariate.

#### Cost-Effectiveness Analyses

A cost-effectiveness analysis will be conducted by comparing the costs and effects of the D(o)epression Blended condition in this study to the costs and effects and effects of D(o)epression face-to-face and TAU. The economic evaluation will be executed in accordance with the CHEERS (Consolidated Health Economic Evaluation Reporting Standards) Statement [50,51], which has been successfully executed previously in an economic evaluation of treatment of anxiety disorders in children [52]. The costs of blended CBT versus face-to-face CBT and TAU will be expressed in (1) incremental costs per adolescent with a depression in full remission (based on the K-SADS-PL) and (2) incremental costs per quality-adjusted life year (based on the EuroQol). To gain insight into the uncertainty surrounding subtotal and total costs, and due to highly skewed cost distributions, bootstrap simulations (1000 replications) will be conducted. Bootstrap simulations will be conducted to quantify the uncertainty around the incremental cost-effectiveness ratio [53], yielding information about the joint distribution of cost and effect differences. The bootstrapped cost-effectiveness ratios will be subsequently plotted in a cost-effectiveness plane. The bootstrapped incremental cost-effectiveness ratios will also be depicted in a cost-effectiveness acceptability curve showing the probability that a condition is cost-effective using a range of ceiling ratios. Also, sensitivity analyses will be performed to test the robustness of the results. The cost-effectiveness analyses will be done separately from a mental health perspective and a societal perspective over a period of 6 months and 1 year.

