### Cost-Effectiveness Measures

Health-related quality of life will be measured with the Dutch version of the EuroQol Questionnaire (EQ-5D-Y) [35] and with the parent-rated EuroQol Questionnaire (EQ-5D proxy version) [35], which will be used to calculate quality-adjusted life-years.

The economic evaluation will be performed by registration of health care usage and costs in a cost questionnaire with a recall period of 3 months, which will be filled out by parents (which is identical to the one used in the previous RCT). Health care usage and registered costs that will be assessed are direct health care costs (eg, costs of psychologist, general practitioner, online treatment program, and medication), direct non-health care costs (eg, informal care), indirect costs (eg, monetary value of production losses caused by absence and reduced productivity and school), and out-of-pocket costs (eg, own contribution and transport costs). Costs will be calculated from a mental health care view and a societal view. The units of health care usage (eg, contact with the general practitioner, a session with a psychologist, costs of the online program) will be multiplied by the standard cost price obtained from the Dutch costing manual [36].

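### The cost-effectiveness analysis of a non-randomised comparison specifies no adjustment for baseline utility, baseline costs or confounders, so baseline imbalance can pass partly into the incremental QALYs and costs

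*Protocol article*

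**What the plan says.** The Cost-Effectiveness Analyses section sets out the contrast: "comparing the costs and effects of the D(o)epression Blended condition in this study to the costs and effects" of face-to-face CBT and treatment as usual, both taken from the earlier randomised trial. It fixes two effect measures (full remission on the K-SADS-PL, and QALYs from the EuroQol), 1000 bootstrap replications, two perspectives and two horizons. On uncertainty it says "Bootstrap simulations will be conducted to quantify the uncertainty around the incremental cost-effectiveness ratio", and it adds that "sensitivity analyses will be performed to test the robustness of the results" without giving their content. It names no covariate, regression model or weighting.

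Four other places bear on the point:

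- **Analysis of Secondary Outcomes:** quality of life is among the outcomes whose intervention effect "will be evaluated using linear mixed modeling with the baseline level of the concerning variable as the covariate".
- **Preliminary Analyses:** the screen covers "Possible baseline differences in demographic and diagnostic characteristics between the three conditions". The rule that follows is "If these variables show differences between the conditions, they will be entered as covariates in all models and regression models to test the effectiveness".
- **Cost-Effectiveness Measures and Table 1:** costs come from "registration of health care usage and costs in a cost questionnaire with a recall period of 3 months". Table 1 schedules the cost diary at T0, T3, T4 and T5, and the EQ-5D-Y at all six assessments, T0 included.
- **Strengths and Limitations:** "Since there is no randomization in the current trial, it cannot be ruled out that there are slight differences in the participants, therapists, or societal" (the quote stops one word short of the sentence's end).

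**The concern.** The blended cohort is new and its comparators are historical, so baseline utility and prior resource use need not be balanced. Both predict what follows: patients who start with better utility tend to have better utility later, and patients who used more care before entry tend to use more afterwards. A plain difference in QALYs or costs therefore mixes treatment effect with case mix. Bootstrapping describes sampling variability around that difference. It does not move the estimate, so the cost-effectiveness plane and acceptability curve could look precise while centred in the wrong place.

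The plan also treats one instrument in two ways. The EuroQol as quality of life is adjusted for its T0 value, while the EuroQol as QALYs has no stated adjustment. The article could then report no adjusted effect on quality of life beside an apparent QALY gain.

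Cost-effectiveness is named with effectiveness in the objective, and the Implications for Practice section makes wide implementation depend on both.

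**Working it through.** The plan gives no figure on this point and no standard deviation for utility or costs, so there is nothing of its own to reproduce. The check has three steps.

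**1. Does any stated rule supply the adjustment?**

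- The secondary-outcome model adjusts quality of life, but QALYs and costs are not on its list.
- The Preliminary Analyses rule screens demographic and diagnostic characteristics. EQ-5D utility and prior three-month costs are not named and do not fall naturally under either word.
- Its covariates go into models of effectiveness, whereas the article elsewhere names effectiveness and cost-effectiveness separately. The phrase about all models leaves room for a wider reading, so its reach is unclear.
- The rule acts only on observed differences. Suppose that means a two-sided 5% test between two conditions (assumed). The chance of flagging an imbalance of d SD is Φ(d·√(n1·n2/(n1+n2)) − 1.96). With 44 in a control arm (Abstract) and 70 planned (Sample Size) or 42 recruited (Recruitment) in the blended cohort:
  - 70 vs 44: √(70·44/114) = 5.198. Power is 34% for d = 0.3 and 74% for d = 0.5.
  - 42 vs 44: √(42·44/86) = 4.636. Power is 28% for d = 0.3 and 64% for d = 0.5.

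Even on the wider reading, moderate imbalances would often go unadjusted.

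**2. How much of a utility gap reaches the QALY difference?**

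Assumptions: QALYs are the area under the EQ-5D curve over one year from T0 (the article gives no formula). There is no treatment effect. Utility at every later assessment regresses on T0 utility with the same slope b. T1 is at 5 weeks, as in Table 1.

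- Weight of the T0 value in the trapezoid: w = (5/52)/2 = 0.048.
- Share of the gap carried over: w + (1 − w)·b. Because b is the same at every later assessment, the timing of T2 to T5 drops out.
- b = 0.3: 0.048 + 0.952·0.3 = 0.334.
- b = 0.7: 0.048 + 0.952·0.7 = 0.714.

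Spurious QALY difference, by assumed baseline gap:

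| Gap | b = 0.3 | b = 0.7 |
|---|---|---|
| 0.02 | 0.007 | 0.014 |
| 0.05 | 0.017 | 0.036 |
| 0.10 | 0.033 | 0.071 |

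A simulation with 42 vs 44 patients and utility SD 0.20 (assumed) agrees closely: 0.0167 and 0.0358 for the 0.05 gap. Regression of QALYs on condition and T0 utility reduced the difference to about 0 in every setting. It does so because, by construction, the gap acts only through T0 utility.

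**3. In money.** For the 0.05 gap at an assumed EUR 20,000 to 80,000 per QALY: 0.0167 × 20,000 ≈ EUR 330, and 0.0357 × 80,000 ≈ EUR 2,860 per patient.

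The same mechanism applies to costs, but nothing in the article allows its size to be estimated.

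**The case against.** The strongest reply is that silence is not a statement. A reader might infer that the plan commits to raw, unadjusted differences. It does not: the section never uses those words, and a bootstrap works equally well around adjusted differences. The article condenses a fuller protocol, a separate health-economic plan may exist, and covariate sets are often left to such documents. The covariate rule mentions all models, and the effects in the economic analysis are remission and QALYs, so it could be read to reach them. Sensitivity analyses are promised.

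Much of this stands. It cannot be said that an unadjusted analysis is planned, nor that confounders are certainly ignored. What remains is that this section is otherwise specific, and that the article fixes baseline adjustment for the EuroQol in one analysis while specifying none in the other. The covariate rule, even read widely, names neither utility nor costs and depends on observed differences. Sensitivity analyses without stated content commit to nothing.

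A reader might also infer that an imbalance passes in full into the cost-effectiveness ratio. It does not: on the assumed slopes, one third to about 70% of a utility gap is carried over.

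**Conclusion.** The concern holds in this form: for a comparison with historical arms, the cost-effectiveness section specifies no adjustment for baseline utility, baseline costs or confounders, and the general covariate rule does not clearly supply it. Followed as written, the analysis can carry baseline imbalance partly into the incremental QALYs and costs without the bootstrap showing it.

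The figures (0.017 to 0.036 QALY, EUR 330 to 2,860 per patient) illustrate the mechanism and do not predict its size here. The utility gap, the slope, the area-under-the-curve QALY and the euro values are all assumed, and the bias could favour either condition. The article does not show that the cohorts differ, only that its authors accept that they may. This should be settled before the cost and outcome data are compared. If a fuller plan already specifies the adjustment, a sentence pointing to it would resolve the matter.

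**What to change.** State in the Cost-Effectiveness Analyses section that, within each bootstrap replicate:

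- incremental QALYs are estimated by regression on condition and T0 EQ-5D utility;
- incremental costs are estimated by regression on condition and T0 three-month costs;
- the same pre-specified confounders enter both models and the model for the remission effect measure, whatever baseline significance tests show.

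Build the ratio, plane and acceptability curve from these adjusted differences, and report the unadjusted comparison as a sensitivity analysis.

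The cost is one paragraph of text and modest extra programming. Both baseline measures are already scheduled at T0, so no new data are needed. The price in method is some model dependence, and adjustment removes only imbalance in what was measured. Differences in therapists or period between the cohorts remain a limitation.
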